### Intervention measures

Children in the ASER group are required to consume no more than 30–35% of their target total daily energy intake during the period from after-school (17:30) until bedtime. The target total energy intake during the weight loss phase is based on the age-appropriate estimated energy requirement for healthy children, reduced by 300–500 kcal. Dinner must begin no later than 19:00 local time. Energy intake is not restricted during other time periods, but healthy eating guidance is provided, including recommended portions of fruits, vegetables, and dairy products to ensure adequate nutrition.

Dietitians will calculate dinner and post-dinner snack portions based on each child’s eating habits and the Acceptable Macronutrient Distribution Ranges (AMDR) recommended for children [40], and will develop individualized dietary plans. Nutrition education will be provided to the caregivers using food models or photographs. Caregivers are advised to weigh foods during meal preparation and to keep detailed records. To enhance compliance, one evening per week may be designated as a “free day,” during which energy intake is not strictly restricted.

The first 12 weeks constitute the intensive intervention phase, followed by a maintenance phase from weeks 13 to 24. In the first week, caregivers are required to record and submit daily dietary logs and food photographs via a designated WeChat group, with particular emphasis on the period from after-school to bedtime, to facilitate monitoring and guidance by the research team.

During the intensive intervention phase, dietary intake will be assessed at weeks 4 and 8 using 24-h dietary recalls. At these interim visits, participants will also receive face-to-face guidance, health education, and anthropometric measurements. In the maintenance phase, participants are expected to continue following the prescribed dietary plan.

Participants in the control group will receive standard clinical dietary advice for weight management based on the Nutritional Guidelines for Weight Management of School-Aged Children [35], which include recommendations on energy intake and healthy dietary patterns. The mode and frequency of feedback and supervision will be consistent with those of the intervention group. Both groups will receive regular health education on lifestyle topics, including balanced nutrition, physical activity, and sleep hygiene. Comprehensive assessments, including food frequency questionnaires (FFQ), 24-h dietary recalls, anthropometric measurements, body composition analysis, laboratory tests, and relevant questionnaires, will be conducted at baseline (week 0), week 12, and week 24. During the study period, participants will be asked not to engage in any additional weight-loss interventions, including other dietary programs, medications, or structured exercise regimens outside of their usual activities. Routine pediatric care and non-weight-related treatments will be allowed.

### Outcomes

All outcome data will be collected and analyzed by certified evaluators who are blinded to treatment allocation.

#### Primary outcome

The primary outcome is the between-group difference in body mass index *z*-score (BMIz) change at week 12 (ASER group vs. control group).

#### Secondary outcomes

Body weight and body composition indicators:BMIz: Between-group differences at week 24; within-group changes from baseline at weeks 12 and 24.Degree of reduction in %BMI_95_ (≥ 5%, ≥ 10%, and ≥ 15%), waist-to-height ratio, and body composition parameters (fat mass index [FMI], fat-free mass index [FFMI], visceral fat area, body fat percentage): between-group and within-group changes at weeks 12 and 24.Growth and developmental indicators:Height, Tanner stage, annual growth velocity (GV), and height SDS changes from baseline, with between-group comparisons at weeks 12 and 24.GV (cm/year) = 12 * (current height – previous height)/(visit interval in months).Height SDS is calculated based on data from the 2005 Chinese National Growth Survey in nine cities [41]: Height SDS = (height at assessment time − mean height for same age/gender group)/standard deviation of height for same age/gender group).IGF-1 changes from baseline and between-group comparisons at week 24.Cardiometabolic risk factors and serum biochemical indicators:Blood pressure; serum biochemical indicators (high-sensitivity C-reactive protein, liver function, renal function, uric acid); lipid profile (total triglycerides, HDL-C, LDL-C); blood glucose at 0, 60, and 120 min during the oral glucose tolerance test (OGTT); insulin release test (IRT); area under the curve (AUC) for OGTT and IRT; homeostasis model assessment of insulin resistance (HOMA-IR) and β-cell function (HOMA-B): between-group and within-group changes at weeks 12 and 24Dietary and psychobehavioral parameters:Dietary quality (dietary balance index, dietary inflammatory index, etc.), dietary patterns, sleep, anxiety levels, and physical activity: between-group and within-group changes at weeks 12 and 24.Adverse events (AEs):AEs will be systematically monitored and recorded throughout the trial. Expected AEs in this low-risk intervention are mild.Between-group differences in the incidence of all AEs at weeks 12 and 24.

### Questionnaire survey

Trained investigators who are blinded to group allocation will collect data using validated questionnaires to assess personal information (e.g., name, sex, age), medical history, intake of macronutrients and energy, daily physical activity, sleep patterns, and anxiety levels. Dietary quality and patterns will be evaluated using 24-h dietary recall, food frequency questionnaires (FFQ), and indices such as the dietary balance index (DBI) and the dietary inflammatory index (DII).

### Anthropometric and blood pressure measurements

Height and weight will be measured by trained assessors blinded to group allocation. Height will be measured to the nearest 0.1 cm using a calibrated wall-mounted stadiometer, and body weight will be measured to the nearest 0.1 kg using a calibrated digital scale at each study visit. Waist circumference will be measured at the midpoint between the lowest rib and iliac crest using a standard, non-stretchable measuring tape to the nearest 0.1 cm, with participants standing upright at normal expiration. All anthropometric measurements, including height, weight, and waist circumference, will be taken twice, and the average of the two readings will be used for analysis.

Blood pressure will be measured under standardized conditions by trained, blinded assessors using an automated oscillometric device (Omron, Japan). At least two readings will be taken at 1–2-min intervals, and the mean of the two readings will be used for analysis. If the difference between the first and second readings exceeds 5 mmHg, a third measurement should be taken. The average of all three readings should then be recorded as the final result.

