### Quality control and data management

Data will be collected using paper Case Record Forms (CRFs). Prior to participant enrollment, all study personnel will receive standardized training to ensure proper understanding of study procedures and data recording requirements. Data will be recorded by trained investigators in real time, followed by independent double-checking by two individuals to ensure completeness and logical consistency of the forms. Data entry will be performed using a double-entry system. Upon completion, consistency checks will be conducted. Any discrepancies or abnormal values will be traced back to the original records for verification and correction. All participants will be identified using unique study codes. The linkage between personal information and study codes will be stored separately, accessible only to authorized research staff for necessary identification. All paper-based data will be securely stored in designated cabinets, with no access granted to unauthorized personnel. The hospital’s Ethics Committee will oversee the data collection and management process to ensure compliance with ethical guidelines and data protection requirements.

To promote participant retention and adherence to the follow-up schedule, regular reminders (e.g., phone calls or text messages) will be provided before each study visit. Participants and their guardians will receive educational support and periodic feedback regarding progress. Concurrent health education sessions during visits will reinforce engagement and study goal understanding. For participants who withdraw or deviate from the intervention protocol, efforts will be made to collect primary and secondary outcome data at all available time points, particularly at the 12-week and 24-week assessments.

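### Two height readings are averaged however far apart they are, while blood pressure gets a tolerance and a third reading; half of a gross height error stays in BMIz and growth velocity (noise, low priority)

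*Protocol article*

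**What the plan says.** In the section on anthropometric and blood pressure measurements, the article gives the rule for height, weight and waist: they "will be taken twice, and the average of the two readings will be used for analysis". It names no maximum difference and no repeat. On precision and conduct it says "Height will be measured to the nearest 0.1 cm using a calibrated wall-mounted stadiometer" and "Height and weight will be measured by trained assessors blinded to group allocation".

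The next paragraph treats blood pressure differently: "If the difference between the first and second readings exceeds 5 mmHg, a third measurement should be taken". It continues: "The average of all three readings should then be recorded as the final result".

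Height and weight carry the main result (Primary outcome: "The primary outcome is the between-group difference in body mass index" z-score change at week 12). Height also feeds the growth outcomes. Under Secondary outcomes, growth velocity is defined as "GV (cm/year) = 12 * (current height – previous height)/(visit interval in months".

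Under Quality control and data management, two people check the forms for completeness and logic, data are entered twice, and "Any discrepancies or abnormal values will be traced back to the original records for verification and correction". No re-measurement of the child is mentioned.

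**The concern.** The protocol states a complete rule for the analysis value, and that rule does nothing when two readings disagree. If one height is wrong because of posture or a misread scale, the mean keeps half of the error. Height enters BMI squared, and 12-week growth velocity turns a small height difference into an annual rate. Blood pressure, one of many secondary outcomes, is protected against a discordant pair; the measurement behind the primary endpoint is not.

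A record check can correct a transcription slip. It cannot recover a true height once the child has left, because the paper form holds the same two numbers. At stake are some extra variance in the primary comparison and, more visibly, individual growth velocities that cannot be trusted.

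**Working it through.** **Inputs from the article.** Planned difference in BMIz change 0.14, SD 0.28, two-sided alpha 0.05, 82 per group, 20% dropout (Sample size estimation); the reading rules and the growth velocity formula quoted above.

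**Assumptions not in the article.** Height 140 cm and BMI 25, so weight = 25 × 1.40² = 49 kg. Reading SD 0.3 cm. Gross errors of 2-5 cm, random sign, in 1-2% of single readings. 0.3 BMIz per kg/m² (range 0.2-0.4).

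**Baseline power.** The article has no figure of its own on this point. Completers per arm are 82 × 0.8 = 65.6, and a two-sided normal test then has 81.7% power. That is below the stated 85%: 72 per arm are needed, and 72/0.8 = 90 per arm, 180 in total rather than 164. This is a separate matter; 81.7% serves here only as the starting point.

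**One child, BMIz.** A 2 cm fault in one of two readings leaves 1 cm in the mean. BMI shift = 49/1.40² − 49/1.41² = 0.353 kg/m². At 0.2-0.4 z per kg/m² that is 0.07-0.14 BMIz, or 0.25-0.5 of the individual SD of 0.28. A second conversion, using a BMI coefficient of variation of 0.10-0.15 and heights of 130-150 cm, gives 0.09-0.15.

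**One child, growth velocity.** Twelve weeks are 84/(365.25/12) = 2.76 months, so the multiplier is 12/2.76 = 4.35 per cm.

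| Fault in one reading | Left in mean of two | Error in 12-week GV | Left in mean of three | Error in 12-week GV |
|---|---|---|---|---|
| 1 cm | 0.50 cm | 2.17 cm/year | 0.33 cm | 1.45 cm/year |
| 2 cm | 1.00 cm | 4.35 cm/year | 0.67 cm | 2.90 cm/year |

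For scale, an assumed growth of 5-6 cm/year is 1.2-1.4 cm in 12 weeks.

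**Trial level, BMIz (simulation).** The error in BMIz change is (week-12 height error − baseline height error) × 2 × 25/140 × z per kg/m². Its variance is compared with 0.28² = 0.0784. The fix is a third reading when the first two differ by more than 1.0 cm.

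| Rule | Share of 0.0784 at 0.3 z per kg/m² | Range over 0.2-0.4 |
|---|---|---|
| Mean of two (stated) | 3.2-5.1% | 1.4-9.1% |
| Third reading, mean of three | 2.2-3.1% | not tabulated |
| Third reading, median | 1.4-1.6% | 0.6-2.8% |

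Take 0.28 as already containing the error. With 1% gross errors, the median rule gives SD = 0.28 × √(1 − 0.032 + 0.014) = 0.277 and power 82.4%. With 2%, SD = 0.28 × √(1 − 0.051 + 0.016) = 0.275 and power about 83.0-83.1%, depending on rounding. The gain is about 0.7-1.4 points. A separate calculation that adds the error on top of 0.28 points the same way: 2 cm faults at 5% of visits take power from 81.7% to 81.1%, and one child with such a fault moves the group difference by about 0.114/65.6 = 0.002.

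**Trial level, growth velocity.** In the same simulation, 4.0-7.4% of children have a 12-week value wrong by more than 4 cm/year under the stated rule and 0.3-0.4% under the median rule. A hand check agrees. An error of 4 cm/year needs 4/4.35 = 0.92 cm of height error, and the chance that at least one of four readings is faulty is 1 − 0.99⁴ = 3.9% to 1 − 0.98⁴ = 7.8%.

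**Workload.** Ordinary noise alone puts two readings more than 1.0 cm apart in about 1.8% of pairs (SD of the difference 0.3 × √2 = 0.42 cm). Gross errors add 1 − 0.99² = 2.0% to 1 − 0.98² = 4.0%. The total is about 4-6% of height measurements.

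**The case against.** The strongest reply is that averaging two readings by trained, blinded assessors on calibrated equipment is ordinary practice, and that different repeat rules for height and blood pressure are no contradiction. That is right: the point concerns a stated rule that could be better, not an inconsistency. A measurement manual that is not shown may also hold a tolerance. Against this, the article states the analysis value for height without exception and prints the blood-pressure tolerance directly after it.

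Other safeguards deserve credit. Two people check each form for logical consistency, and height is also taken at the interim visits at weeks 4 and 8, so a gross error may be noticed. But the article gives neither the timing of the check nor any re-measurement, so noticing an error does not restore the value.

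The gross-error rate is assumed and drives the result. The planned SD was informed by prior studies and may already contain measurement error, so the plan may already absorb some of this noise. The proposed tolerance does not remove ordinary reading noise either: 0.3 cm per reading gives a 12-week growth velocity error with SD of about 0.3 × 4.35 = 1.3 cm/year under any of these rules. All of this stands, and it is why the point is low priority.

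**Conclusion.** The point holds as a minor measurement-quality improvement. The stated rule keeps half of a gross height error, and nothing in the article would recover a height misread at the visit. The effect on the primary comparison is about 0.7-1.4 points of power at 0.3 z per kg/m² if 1-2% of single readings are off by 2-5 cm, and close to none if such errors are rare. The clearer gain is in individual 12-week growth velocity: about 4-7% of children wrong by more than 4 cm/year, against 0.3-0.4%, on the same assumed rate. No size has been worked out for weight or waist.

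A reader might infer three stronger things that the article does not support:

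- **The primary comparison is biased.** Assessors are blinded, so there is no reason to expect the error to differ by arm.
- **A single bad height can cancel the planned effect, since 0.07-0.14 BMIz is close to 0.14.** That sets one child's error against a difference between group means; one such child moves that difference by about 0.002.
- **The blood-pressure rule would cure the problem.** It averages all three readings and so keeps a third of the fault.

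**What to change.** In the section on anthropometric and blood pressure measurements, add: if the two height readings at a visit differ by more than a pre-set tolerance (for example 1.0 cm), the same blinded assessor takes a third reading at that visit, and the median of the three is used. Apply it at all visits and in both arms. The investigators should set analogous limits for weight and waist. Use the median and not the mean of three, because the median discards a single outlying reading. If the measurement manual already holds such a rule, one sentence saying so is enough.

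Cost: one sentence, one extra CRF field and a brief repeat reading at about 4-6% of height measurements under the assumptions above. No added visits or staff are needed.

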### Laboratory assessments

All blood samples will be collected by trained and blinded nurses at the First Affiliated Hospital of Guangxi Medical University following standard operating procedures. Participants will be required to fast overnight (≥ 10 h) prior to sampling. All laboratory analyses will be performed at KingMed Diagnostics, a qualified third-party medical testing center, using the following validated methods described below. For the oral glucose tolerance test (OGTT) and insulin release test (IRT), fasting blood samples will be collected first. Within 5 min, participants will ingest 1.75 g of glucose per kilogram of body weight (not exceeding 75 g), dissolved in 250 mL of water. Subsequent blood samples will be drawn at 60 min and 120 min after glucose ingestion.

Plasma glucose concentrations will be measured using the hexokinase enzymatic method (Mindray, China). Glycated hemoglobin (HbA1c) will be measured by high-performance liquid chromatography (HbA1c Analyzer, Lifotronic Technology, China). Serum insulin levels will be assessed using a chemiluminescence immunoassay (Mindray, China). Insulin-like growth factor 1 (IGF-1) will be measured using liquid chromatography-tandem mass spectrometry (LC-MS/MS; Thermo Fisher Scientific, USA). High-sensitivity C-reactive protein (hs-CRP), liver enzymes, renal function markers, uric acid, and lipid profile will be analyzed using an automated biochemical analyzer (Mindray, China).

Additionally, with participant consent, certain specimens (including whole blood and serum) will be stored at − 80 °C for potential future studies, such as metabolomics or transcriptomic sequencing. These future studies have not yet been determined, and the use of stored samples will depend on specific research needs. This has been clearly outlined in the informed consent form. Any future use of the samples for related analyses will require separate approval from the ethics committee, and results from exploratory analyses will be reported independently from the main study findings.

### Body composition and additional assessments

Body composition, including fat mass index (FMI), fat-free mass index (FFMI), visceral fat area, and body fat percentage, will be measured using a bioelectrical impedance analyzer (InBody, South Korea). Electrocardiography (ECG) will be performed to assess for potential arrhythmias or conduction abnormalities.

### Adverse events and safety monitoring

No formal interim analyses or stopping guidelines are planned; all data will be analyzed post-follow-up. However, the principal investigator (PI) will suspend the trial immediately if ≥ 3 intervention-related serious AEs (SAEs) occur in one group, with final termination requiring PI and IRB consensus. This ensures participant safety while aligning with predefined secondary endpoints for AE incidence.

An adverse event (AE) is defined as any unfavorable sign, symptom, or medical condition that arises after the initiation of the study intervention. Pre-existing medical conditions or diseases will only be considered AEs if they worsen after the start of the intervention. Unchanged pre-existing conditions will not be classified as AEs. Abnormal laboratory findings will not be considered AEs unless deemed clinically significant by the investigator.

At each clinical visit, the investigator (or a designated staff member) will assess whether any AEs have occurred. If a participant is unable to continue in the study due to an AE or other unavoidable reason, the intervention will be discontinued. Reasons for discontinuation may include gastrointestinal symptoms or growth and developmental issues that, in the opinion of the physician, warrant termination of the intervention.

All AEs will be evaluated and managed by the participant’s physician and monitored until resolution to ensure participant safety. AEs will be systematically documented according to standardized procedures. The incidence of AEs is predefined as a secondary endpoint to support a comprehensive benefit-risk assessment of the intervention.

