### Randomization and allocation

Eligible participants will be randomized 1:1 to the ASER or control group using centralized, computer-assisted minimization with allocation concealment, balancing age (8–9 years vs. 10–11 years), sex (male vs. female), and baseline BMI *z*-score category (mild: + 1.645 ≤ z < + 2.5; moderate: + 2.5 ≤ z < + 3.0; severe: z ≥ + 3.0). To avoid treatment contamination, related participants from the same family will be allocated to the same intervention group. Randomization will be implemented by an independent statistician via a secure system; site investigators will enroll participants, submit baseline stratification variables, and receive the assignment, with the allocation sequence concealed from site staff until assignment. Due to the nature of the intervention, blinding of participants and intervention implementers is not feasible. However, health education physicians, data collectors, and outcome assessors/statisticians will remain blinded to group assignments throughout the study.

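### The protocol promises blinded collection of all outcomes but does not say whether those who elicit and classify adverse events, a between-group secondary endpoint, are blinded; as written they may know the arm.

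*Protocol article*

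**What the plan says.** All references are to the protocol article.

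- **Endpoint status.** Secondary outcomes lists "Between-group differences in the incidence of all AEs at weeks 12 and 24". The section on adverse events and safety monitoring repeats that AE incidence is a secondary endpoint, and Statistical analysis tests it with chi-square tests and logistic regression.
- **General blinding claim.** Outcomes opens with "All outcome data will be collected and analyzed by certified evaluators who are blinded to treatment allocation".
- **Who learns the arm.** Randomization and allocation says that "site investigators will enroll participants, submit baseline stratification variables, and receive the assignment". It adds that "blinding of participants and intervention implementers is not feasible".
- **Who stays blinded.** The same section says that "health education physicians, data collectors, and outcome assessors/statisticians will remain blinded to group assignments throughout the study". Investigators are not on that list.
- **Who elicits AEs.** Adverse events and safety monitoring: "At each clinical visit, the investigator (or a designated staff member) will assess whether any AEs have occurred".
- **Who decides whether a laboratory abnormality is an AE.** Same section: "Abnormal laboratory findings will not be considered AEs unless deemed clinically significant by the investigator".
- **Later checks.** Oversight and monitoring rules out an endpoint adjudication committee.

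**The concern.** Recording an AE involves at least two judgements: whether something a child or caregiver mentions is an event, and whether an out-of-range laboratory value matters clinically. Both determine the numerator of a comparative endpoint. If the person judging knows the arm, optimism about the new diet can lower the ASER count and extra vigilance can raise it, with no true difference between arms.

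The AE comparison is meant to support the benefit-risk assessment. The Discussion presents blinded evaluators as a strength and names as a limitation only the open-label design and unblinded participants, in relation to self-report. A reader of the results would therefore take the AE comparison to be observer-blind, and the AE section does not secure that.

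**Working it through.** **1. Comparing the sections**

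| Section | Data or task | Who | Blinding stated? |
|---|---|---|---|
| Outcomes | all outcome data | certified evaluators | yes, blinded |
| Randomization and allocation | enrolment, receipt of assignment | site investigators | they receive the arm |
| Questionnaire survey | questionnaires, medical history | trained investigators | yes, blinded |
| Anthropometric and blood pressure measurements | height, weight, blood pressure | trained assessors | yes, blinded |
| Laboratory assessments | blood sampling | nurses | yes, blinded |
| Adverse events and safety monitoring | whether an AE occurred | investigator or designated staff member | not stated |
| Adverse events and safety monitoring | whether a laboratory abnormality is an AE | investigator | not stated |
| Adverse events and safety monitoring | evaluation and management of AEs | participant's physician | not stated |

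Two readings are possible.

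- *The AE investigator is one of the site investigators who receive the assignment.* Then the sentence in Outcomes is untrue for AEs.
- *The AE investigator is one of the blinded investigators of the Questionnaire survey section.* Then the AE section omits the one fact that protects the endpoint.

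The first is more likely: investigators are absent from the list of blinded roles, and the sections on questionnaires, measurements and blood sampling state blinding where the AE section does not. The text does not settle it. Under either reading a correction is needed.

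**2. Size: illustration only**

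The document gives no AE rate and no basis for a rate of misclassification, so there is no planned figure to reproduce. The only input from the plan is 82 children per arm. Everything else here is assumed.

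*Effect on the estimate.* Take a true incidence of 15% in both arms: 0.15 × 82 = 12.3 events per arm.

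- 10% of ASER events not recorded: 12.3 × 0.90 = 11.1; risk ratio 11.1 / 12.3 = 0.90.
- 33% not recorded: 12.3 × 0.67 = 8.2; risk ratio 8.2 / 12.3 = 0.67.

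With full recording in the other arm, the apparent risk ratio equals the recorded fraction whatever the true incidence. Over-recording in ASER would push it above 1.

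*Effect on the test.* Let the true incidence p be equal in both arms, with fractions s1 and s2 of events recorded. Observed rates are p × s1 and p × s2. The chance of a nominally significant result in the spurious direction is Φ[(d − 1.96 × se0) / se1], where d is the observed difference, se0 the pooled and se1 the unpooled standard error, with 82 per arm. With equal recording this is 2.5%.

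| p | s1 / s2 | Observed rates | Difference | Significant in that direction |
|---|---|---|---|---|
| 10% | 0.9 / 0.8 | 9% vs 8% | 1 point | 4% |
| 20% | 0.9 / 0.7 | 18% vs 14% | 4 points | 10% |
| 40% | 0.9 / 0.6 | 36% vs 24% | 12 points | 39% |

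The false-positive risk runs from slight to large depending wholly on the assumptions. The steadier consequence is a distorted estimate.

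**The case against.** The strongest reply is that the unblinded assessor is inferred from a shared word. The protocol calls some blinded staff investigators, AE incidence stands under Outcomes and so falls under the general blinding sentence, and the designated staff member could be one of the blinded data collectors. This stands as far as it goes: a reader might infer that the protocol plainly gives AE judgement to unblinded staff and so contradicts itself, but it never says that the AE assessor knows the arm. It does not remove the point, because the AE section leaves the matter open while the randomization section gives the arm to a role of the same name.

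A second reply is that laboratory thresholds and symptom checklists belong in the full protocol, which is not shown. That also stands, and their absence from the article is not counted as an error. The point rests on two statements that the article does make and does not reconcile.

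Third, a reader might infer that the AE comparison carries the case that ASER avoids undernutrition. The documents do not support that. Growth velocity, height SDS, IGF-1, fat-free mass index and liver and renal function are compared separately, and a laboratory abnormality not labelled an AE still enters the laboratory comparisons. Nor does the protocol call the expected AEs subjective; it calls them mild, and it mentions gastrointestinal and growth problems only as possible reasons for stopping the intervention.

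Finally, families know their allocation, so blinded elicitation cannot remove reporting bias, and the Discussion already concedes bias from self-report. True, but observer judgement is a separate source, and it can be reduced.

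**Conclusion.** The point holds as an unreconciled statement about who is blinded, with a credible route to bias in a secondary endpoint. The blinding of the AE assessor is unstated and probably absent; that is an inference from the role descriptions, not something the text shows. Judgement decides what enters the AE numerator, and no adjudication follows. Bias could run in either direction, and its size cannot be derived from the document; the risk ratios and rejection rates above depend on assumed incidences and recording fractions. The primary endpoint is not affected. The correction should be made because it is cheap and uses staff already planned.

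**What to change.** Reconcile Randomization and allocation, Outcomes, Questionnaire survey, and Adverse events and safety monitoring, in one of two ways.

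1. **Preferred: blind the endpoint judgement.** For the AE endpoint, have the blinded data collectors already in the plan elicit AEs at each visit with one symptom checklist, worded identically in both arms. Have a blinded evaluator decide whether each abnormal laboratory value is clinically significant, working from reports without arm labels. Name these roles in the AE section.
2. **Otherwise: narrow the claim.** Limit the sentence in Outcomes to outcomes that are truly assessed blind, and list unblinded AE ascertainment among the limitations in the Discussion.

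Relatedness assessment, the suspension rule and all care decisions stay as they are.

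The first option costs some protocol wording, a one-page checklist and a few minutes per visit. It leaves reporting bias from unblinded families in place, which the limitations should say. The second costs only wording but leaves the observer bias itself untouched.
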